### Sampling methods

For proportionate representation, the proportion ‘p’ will be computed as shown in equation 2, depending on the number of medical trainees each hospital received during the year that preceded the study.

(2)
$$p=\mathrm{sample}\left(n\right)x\frac{100}{\mathrm{Population}\left(N\right)},$$

This means that ~26.7% of each hospital’s annual trainees intake will be recruited, resulting in 321 participants from Kiryandongo, 65 from Jinja, and 47 from Hoima regional referral hospitals.

For the case of law enforcement professionals, the selection will be purposive where the regional police in-charge of traffic will be asked to nominate 22 participants, which is approximately the average number of serving officers at the headquarters for each region, totaling to 66, targeting police stations on main highways leading to the respective municipalities where the study sites are located. Those who consent to participate will then be randomly assigned to join the medical trainee teams. The assignment will be that only 1–2 traffic officers attend a particular training until the required number is attained so as not to strain the police workforce.

### Inclusion criteria

We shall include participants who meet the following criteria: road-traffic police officer, medical intern doctor/nurse, medical student enrolled in Bachelor of medicine and Bachelor of Surgery in clinical years (3rd or 5th) who completed or currently is completing the surgical/traumatology clinical rotation, allied health professional trainee enrolled in Bachelor of Nursing Sciences or Bachelor of Clinical Medicine degree program and is involved in the care of the injured patients or attached to the accident and emergency department during the study period.

### Exclusion criteria

We shall exclude participants who know would not complete all modules of the course for foreseeable reasons such as students having an exam on one of the training days or police officers on duty on the day of training as this would have an impact on the overall course evaluation. Such individuals who will not be available on all the possible alternative training dates will be excluded.

### Quality control, study variables, data collection tools, and their validity

A standardized 4th edition of RTTDC will be delivered without modification in which 20 item precourse and postcourse MCQ will be administered to participants based on the 4th edition of RTTDC instructor manual^27^. Video recordings will be used to capture skill-oriented case scenarios. Desirability of this training and its content will be determined using a 5-point-Likert scale (5=strongly agree, 4=agree, 3=neutral, 2=disagree, 1=strongly disagree) on the 16 topics whose reliability were validated earlier^30^. The relevancy of quality improvement, case scenarios, and communication course modules to the study subjects will be rated on a 3-point scale based on their subjective impression as (3=very relevant, 2=relevant, 1=not relevant), in conformity with previous researchers^30^. Postcourse feedback on team performance will be provided in accordance with the standard RTTDC expected trauma technical team member assigned skills and the validated (T-NOTECHS)^29^. Three trainers will consistently deliver each session of the training through out the study period to minimize inter-operator variation. Team members will maintain their team-mates on both training days. Two offsite independent surgeon consultants will evaluate the MCQs while blinded of which is pretraining or post-training test. The marked items will be returned to an offsite study administrator with an MCQ marking guide who will double check the awarded marks prior to data entry and send back any wrongly marked MCQs for remarking. The data will be collected in hard copies and later transferred to the Research Electronic Data Capture (REDCap) tools hosted by the University of Turku. REDCap is a secure, web-based software platform, which provides an intuitive interface for validated data capture and audit trails for tracking data manipulation^31^. Furthermore, the software enables seamless data export and download procedures that are compatible with commonly used statistical packages, while allowing for data integration and interoperability with external sources^32^.

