**Methods::**

Muticenter interrupted time series of prospective interventional trainings, using the rural trauma team development course (RTTDC) model of the American College of Surgeons. A team of surgeon consultants will execute the training. A prospective cohort of participants will complete a before and after training validated trauma related multiple choice questionnaire during September 2019-November 2023. The difference in mean prepost training percentage multiple choice questionnaire scores will be compared using ANOVA-test at 95% CI. Time series regression models will be used to test for autocorrelations in performance. Acceptability and relevance of the training will be assessed using 3 and 5-point-Likert scales. All analyses will be performed using Stata 15.0. Ethical approval was obtained from Research and Ethics Committee of Mbarara University of Science and Technology (Ref: MUREC 1/7, 05/05-19) and Uganda National Council for Science and Technology (Ref: SS 5082). Retrospective registration was accomplished with Research Registry (UIN: researchregistry9490).

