### Training procedure, team construct, and course implementation

On average 12 (6–24) training sessions will be conducted per site between 28th of September 2019 and 28th of November 2023. Cohorts of participants will be enrolled every after 3 months to strike a balance between the average duration of surgical internship deployment by the Ugandan ministry of health which lasts 1–5 months, and the surgery clinical rotations for medical students which lasts 2 months. Furthermore, the effects of the training are presumed to ‘decay’ after this period and the authors project to realize the targeted sample size based on the 3 months interval. However, permission will be sought from the ethical committee to extend the study in case the target sample is not obtained during the approved duration of the study. The mode of delivery and content of the RTTDC training will not be modified. The training will be advertised by hospital administrators and class representatives and eligible participants will be recruited based on first come first serve. The training dates will be selected to suit the designated days for clinical grand rounds and/ or continuous professional development sessions so as not to interfere with the university and hospital daily schedules. The investigators will use student unique numbers from university hospital administrators’ database to randomly assign recruited participants into teams and to ensure that each participant is recruited once. The participating law enforcement professionals who will show up for the training will pick ballot papers randomly to be assigned to the already created medical trainee teams. The chief trainer will be a chief surgeon (HL) who attended the RTTDC instructor course. The surgeon will coach two co-trainers who are master of surgery residents undertaking a traumatology rotation, at the participating hospitals to make a total of three trainers. Since the program is aimed at capacity building, and residents directly supervise interns in Uganda, the research and ethics board approved training of residents as opposed to consultants not to over strain the skeleton specialized staff at the study sites. Interns and residents contribute to 75% of the health workforce in public hospitals in Uganda^8^. The program will be designed for two days, targeting 30 participants with a trainer: trainee ratio of 1:10, which is the maximum permissible for each training session according to the committee on trauma of the American college of Surgeons. For each team task, participants will be grouped into teams of five to role play a surgeon, surgeon assistant/intern, an anesthesiologist/anesthetic assistant, an allied health professional (emergency room nurse/laboratory/imaging personnel), and a rescue police (representing paramedics in Uganda’s settings).

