### Sample size estimation

According to the respective hospital administrators, a total of 1500 medical trainees had been received at the three participating hospitals during the academic year 2018/2019, which preceded the study. Using the hypergeometric formula in equation 1 for determining sample size in smaller populations,

(1)
$$n=\frac{Nz^{2}\mathrm{pq}}{\left[E^{2}\left(N-1\right)+z^{2}\mathrm{pq}\right]}$$

where:

*N* (population size) =1500

Z=1.96 assuming 95% CI.

P and Q are population proportions that will approve or disapprove the promulgation of rural trauma team development training, each assumed to be 50% since these proportions are unknown

E=value of accuracy of the sample proportions (alpha= 0.05) at 95% CI

*n* (sample size)=307. Since, we plan to retain this same cohort of trainees after 3 months of follow-up for purposes of their incorporation into real-world rural trauma teams during the second phase of the project which will run for the next 4 years from the time of postcourse evaluation, and with a projected 10.25% annual loss to follow-up and nonresponse, we shall add 41% to increase internal validity for the entire 4-year period, thus the final minimum sample size for medical trainees will be 433.

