### Statistical analysis

The data will be exported from REDCap to Stata version 15.0 for analysis (StataCorp. 2017. Stata Statistical Software: Release 15. College Station, TX: StataCorp LLC).

We shall test the data for normalcy using the Shapiro–Francia test and normal histogram curves at 95% CI, regarding *P*<0.05 as statistically significant.

If the data are normally distributed, the difference in pretraining and post-training mean scores will be compared using one way analysis of variance (ANOVA) test otherwise nonparametric Friedman test will be used to compare the scores as a measure of knowledge retention, assuming a null hypothesis of no difference. Box plots will be used for data presentation to offer a succinct visual summary of data distribution.

Furthermore, we shall perform Wilcoxon signed rank nonparametric test to examine the difference in the effect the training has on MCQ scores of the various cadres of participants aggregated (3rd year, 5th year, and interns). The median scores for various groups and their corresponding interquartile range will be reported.

The statistical difference in rank sums regarding desirability and relevance of various course themes will be compared between participating cadres using a nonparametric Kruskal–Wallis (H) test.

Lastly, time series regression (ARIMA) models will be used to test for autocorrelation trends in MCQ performance over the study period for the various medical trainee groups.

All the analyses will be performed using Stata 15.0. (StataCorp. 2017. *Stata Statistical Software: Release 15.* College Station, TX: StataCorp LLC); at 95% CI, regarding a 2-tailed *P*-value <0.05 as statistically significant.

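### The named tests and the sample-size formula treat trainees as independent although they are trained in shared sessions; separately, the account of who trains needs reconciling

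*Protocol article*

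**What the plan says.** Training procedure, team construct, and course implementation: an average of 12 sessions per site (range 6 to 24) at three hospitals, each "targeting 30 participants with a trainer: trainee ratio of 1:10". Teams of five stay together on both days. Sampling methods adds one or two police officers per session and sets trainee targets of 321, 65 and 47 for the three sites. Participant recruitment workflow times the second MCQ at 90 days from Day 1, so those trained together fall due together.

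Sample size estimation: a finite-population formula for a proportion, with "Z=1.96 assuming 95% CI" and the approving and disapproving proportions "each assumed to be 50% since these proportions are unknown". The result, 307, is raised by 41% for loss to follow-up and non-response, giving 433. No other inflation is applied.

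Statistical analysis: one-way ANOVA for pre against post scores, or Friedman if the data are not normal; Wilcoxon signed rank for the trainee cadres; Kruskal–Wallis between cadres for desirability and relevance; ARIMA models for autocorrelation over the study period. Significance is set by "regarding a 2-tailed *P*-value <0.05 as statistically significant". None of the tests carries a session, team or site term.

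Trainers: the quality-control section states that "Three trainers will consistently deliver each session of the training through out the study period to minimize inter-operator variation". The training-procedure section staffs the course with a chief surgeon and "two co-trainers who are master of surgery residents undertaking a traumatology rotation, at the participating hospitals". The abstract states: "A team of surgeon consultants will execute the training".

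**The concern.** Trainees in one session share the trainers, the date, the site, the intake and the team exercises. Their score changes and course ratings are therefore likely to be more alike than those of trainees from different sessions. A test or margin that counts every trainee as a separate piece of information then claims more precision than the data hold. The pre-post P-values and the approval proportion behind the sample size are the results at stake.

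The trainer statements are a related but separate matter. If the trainers change between sessions, differences between them add to session-level variation. Clustering would remain even with the same three trainers throughout.

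**Working it through.** **1. The plan's own figures.** Inputs from Sample size estimation: N = 1500, z = 1.96, p = q = 0.5, E = 0.05.

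n = N z² pq / [E²(N − 1) + z² pq] = 1440.6 / (3.7475 + 0.9604) = 306.0 (stated: 307). Then 307 × 1.41 = 432.87, i.e. 433 as stated. The figures reproduce, and the only inflation is for attrition.

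**2. Session size.** Assume 12 sessions at every site, the stated average. The site targets give 321/12 = 26.75, 65/12 = 5.42 and 47/12 = 3.92 trainees per session. The person-weighted size is 12 × (26.75² + 5.42² + 3.92²)/433 = 21.07. The simple mean is 433/36 = 12.0. A full session of 30 less two police officers holds 28.

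**3. Design effect,** DE = 1 + (m − 1) × ICC. The protocol gives no ICC; the values are assumptions.

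| Session size m | ICC 0.02 | ICC 0.05 | ICC 0.10 |
|---|---|---|---|
| 12 | 1.22 | 1.55 | 2.10 |
| 21.1 | 1.40 | 2.00 | 3.01 |
| 28 | 1.54 | 2.35 | 3.70 |

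At m = 21.1 and ICC 0.05, 433 trainees carry the information of about 433/2.00 = 216 independent ones.

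**4. Approval margin.** With all 433 counted as independent: 1.96 × √[(0.25/433) × (1067/1499)] = 0.0397, or ±4.0%. Multiplying by √DE at m = 21.1 gives ±4.7%, ±5.6% and ±6.9%. The ±5% target is passed when DE exceeds (0.05/0.0397)² = 1.58, that is, above an ICC of 0.58/20.07 = 0.029. At m = 12 the threshold is 0.58/11.03 = 0.053.

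**5. Type I error of the named tests at nominal 5%.** For a paired test the approximation is 2[1 − Φ(1.96/√DE)], which gives 9.8%, 16.6% and 25.8% at m = 21.1. A simulation of 433 trainees in 36 unequal sessions (4,000 runs per setting) gave:

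| Test | ICC 0.02 | ICC 0.05 | ICC 0.10 |
|---|---|---|---|
| Wilcoxon signed rank | 9.8% | 16.9% | 24.5% |
| Friedman | 8.5% | 13.8% | 20.8% |
| One-way ANOVA, pre-post correlation ρ = 0.3 | 5.0% | 10.4% | 17.6% |
| One-way ANOVA, ρ = 0.5 | 2.0% | 5.4% | 10.7% |
| One-way ANOVA, ρ = 0.7 | 0.2% | 1.0% | 3.8% |
| Kruskal–Wallis, cadres mixed within sessions | 5.6% | 5.2% | 4.7% |
| Kruskal–Wallis, one cadre per session | 10.9% | 20.5% | 35.4% |

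The ANOVA rows follow from a second error. Treating one person's two scores as independent groups overstates the variance of the difference, so the ratio of true to assumed variance is (1 − ρ) × DE. At m = 21.1 and ICC 0.05 this is 1.40, 1.00 and 0.60 for ρ = 0.3, 0.5 and 0.7. The protocol does not give ρ.

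**6. Trainer statements side by side.** Consultants (abstract) against one chief surgeon plus two residents (training procedure) is a direct contradiction; the latter section also records ethics approval for using residents instead of consultants. The same three people for every session (quality control) against residents on rotation, over three hospitals and September 2019 to November 2023, is a conflict by inference, since the length of the residents' rotation is not stated.

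**The case against.** A reader might infer that every test is too liberal and every interval too narrow. The protocol does not support that. The first-named test, the one-way ANOVA, may be conservative. Kruskal–Wallis holds near 5% when cadres mix within sessions. ARIMA does allow for correlation over calendar time, although not among trainees in one session.

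A reader might also infer that constant trainers are the plan's safeguard against clustering, and that this safeguard fails. The quality-control section offers them only to limit variation between operators. The limitations section names a different safeguard, repeated series at several sites with autoregression models, against time trends and differences between groups. Moreover, the promise of three trainers could mean three in number, not the same three people.

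The size is uncertain too. No ICC is given. Twelve sessions at the smallest site means 3.9 trainees each, fewer than one team of five, so the real session pattern will differ. At ICC 0.02 the approval margin is still inside ±5%.

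Finally, a condensed article may leave variance modelling to an analysis plan. That carries some weight, but this article commits to named tests and a stated precision, and as written neither allows for sessions.

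These objections limit the direction and size of the problem. They leave standing that the paired rank tests and the approval margin are too optimistic under any positive session ICC. That the two ANOVA errors may partly cancel is no defence of that test.

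**Conclusion.** The concern holds in limited form. With positive session correlation, Friedman and signed-rank P-values are too small: type I error is about 8–10%, 14–17% or 21–25% at ICC 0.02, 0.05 or 0.10. The approval margin at 433 becomes ±4.7%, ±5.6% or ±6.9% instead of ±4.0%. For the ANOVA the net direction is unknown, and Kruskal–Wallis is affected mainly if sessions are single-cadre.

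These sizes rest on an assumed ICC, 12 sessions at each site, and paired tests run on all 433 trainees together. Tests within one cadre of mixed sessions would have fewer trainees per session and less inflation.

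The trainer statements need reconciling in their own right. They neither cause nor prove the clustering problem.

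**What to change.** - Analyse each trainee's paired MCQ change (post minus pre), and the acceptability and relevance outcomes, with session-clustered standard errors or a session random effect, and with site as a fixed effect. For MCQ scores the random effect must act on the change. A session intercept on raw pre and post scores alone cancels out of the pre-post difference and leaves its standard error uncorrected. Using the change score also repairs the pairing error in the ANOVA.
- Restate the precision in Sample size estimation with a design effect over a range of ICCs. This does not require enrolling more trainees.
- Reconcile the abstract, the training-procedure section and the quality-control section on who delivers the course, and record the trainer set of each session.

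The cost is revised analysis wording and one recorded field per session. The downside is that some intervals become wider; the MCQ interval may instead narrow relative to the unpaired ANOVA.

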### Statistical analysis

The data will be exported from REDCap to Stata version 15.0 for analysis (StataCorp. 2017. Stata Statistical Software: Release 15. College Station, TX: StataCorp LLC).

We shall test the data for normalcy using the Shapiro–Francia test and normal histogram curves at 95% CI, regarding *P*<0.05 as statistically significant.

If the data are normally distributed, the difference in pretraining and post-training mean scores will be compared using one way analysis of variance (ANOVA) test otherwise nonparametric Friedman test will be used to compare the scores as a measure of knowledge retention, assuming a null hypothesis of no difference. Box plots will be used for data presentation to offer a succinct visual summary of data distribution.

Furthermore, we shall perform Wilcoxon signed rank nonparametric test to examine the difference in the effect the training has on MCQ scores of the various cadres of participants aggregated (3rd year, 5th year, and interns). The median scores for various groups and their corresponding interquartile range will be reported.

The statistical difference in rank sums regarding desirability and relevance of various course themes will be compared between participating cadres using a nonparametric Kruskal–Wallis (H) test.

Lastly, time series regression (ARIMA) models will be used to test for autocorrelation trends in MCQ performance over the study period for the various medical trainee groups.

All the analyses will be performed using Stata 15.0. (StataCorp. 2017. *Stata Statistical Software: Release 15.* College Station, TX: StataCorp LLC); at 95% CI, regarding a 2-tailed *P*-value <0.05 as statistically significant.

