### Specific objectives

To compare the pre-RTTDC and post-RTTDC training scores amongst medical trainees.To determine the relevance and acceptability to promulgation of RTTDC amongst medical trainees and traffic law enforcement professionals in Ugandan rural level III trauma centers.

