### Hypotheses

The null hypothesis of this research protocol is that there is no difference in pre interventional and postinterventional training scores of research participants.

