
### Course outcomes

At the end of the training, participants are anticipated to be able to describe components of their current local trauma system (trauma capacity), describe barriers to effective trauma care in their settings, suggest areas for performance improvement, demonstrate concepts of primary survey and secondary survey, know when to make a timely decision to consult or transfer (referral) for definitive care, and understand the link between lower hospital facilities and regional trauma centers. These goals have been set apriority in accordance with the committee on trauma^27^. The participants will complete a paper based pretraining trauma related MCQs before and at 3 months after the training. The method of data collection will remain the same with a target data completion rate of 100% for every series. The prepost training MCQs will be marked by two independent consultant surgeons who are not part of the research team. The marking team will be blinded by what is pretraining or post-training. Since the answers and marking guide are standardized, we anticipate an inter-rater agreement of 100%.

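### The pre/post MCQ comparison, as written, applies a test for independent samples to paired scores (a conservative error), and its Friedman fallback gives no mean gain or interval

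*Protocol article*

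**What the plan says.** **Pairing.** Course outcomes states: "The participants will complete a paper based pretraining trauma related MCQs before and at 3 months after the training". The abstract describes one cohort tested on both occasions: "A prospective cohort of participants will complete a before and after training validated trauma related multiple choice questionnaire". Sample size estimation adds "we plan to retain this same cohort of trainees after 3 months of follow-up". The Training procedure section uses student numbers "to ensure that each participant is recruited once". Two scores per trainee can therefore be linked.

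**Test.** In Statistical analysis, if the data pass a normality check (Shapiro–Francia plus histograms), "pretraining and post-training mean scores will be compared using one way analysis of variance (ANOVA) test otherwise nonparametric Friedman test" applies. The abstract says: "The difference in mean prepost training percentage multiple choice questionnaire scores will be compared using ANOVA-test at 95% CI". Neither place mentions a repeated-measures form, a subject term or a paired t-test. A paired test, the Wilcoxon signed-rank, appears in the next paragraph, but for the analysis by cadre.

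**Role.** The only stated null hypothesis is that "there is no difference in pre interventional and postinterventional training scores of research participants". The first specific objective is "To compare the pre-RTTDC and post-RTTDC training scores amongst medical trainees". The main objective is feasibility.

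**The concern.** A one-way ANOVA with two levels (before, after) is the unpaired two-sample t-test. It takes the variance of the mean difference to be the sum of two independent variances and leaves out the covariance between a trainee's two scores. A good trainee tends to score well both times, so that covariance is probably positive and the omission makes the standard error too large.

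The fallback has a different weakness. Friedman respects the pairing, but with two occasions it ranks each trainee's scores 1 and 2 and so keeps only the direction of change. It gives a P-value but no mean gain and no interval.

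So neither route delivers a correctly estimated mean change with its 95% CI, for the only hypothesis the protocol states. In practice, a small but real gain retained at 3 months could be reported as no difference, or with an interval wider than the data warrant.

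**Working it through.** **Inputs from the protocol.** Two occasions; 20 items, so one item is 5 percentage points; two-sided α of 0.05; 307 trainees before the allowance for loss and 433 after it.

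**Inputs assumed (not in the protocol).** Within-person correlation ρ of 0.3, 0.5 and 0.7; SD of 15 percentage points, equal on both occasions; approximately normal means.

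**The plan's own figure.** There is no power calculation for the pre/post comparison. The sample size rests on a proportion approving the training: 1500 × 1.96² × 0.25 / (0.05² × 1499 + 1.96² × 0.25) = 306.0, against 307 stated, an immaterial difference. Then 307 × 1.41 = 432.9, which gives 433. These figures serve below only as numbers of pairs.

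**Step 1: standard errors.**
- As written: SE = SD × √(2/n)
- Paired: SE = SD × √(2(1−ρ)/n)
- Ratio: 1/√(1−ρ), whatever n and SD are

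**Step 2: true type I error of the test as written.** 2 × [1 − Φ(1.96/√(1−ρ))]

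| ρ | SE as written, n = 433 (SD units) | Paired SE | Ratio | True type I error |
|---|---|---|---|---|
| 0.3 | 0.0680 | 0.0569 | 1.20 | 1.9% |
| 0.5 | 0.0680 | 0.0481 | 1.41 | 0.6% |
| 0.7 | 0.0680 | 0.0372 | 1.83 | 0.03% |

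At n = 307 the SE as written is 0.0807 SD, against 0.0675, 0.0571 and 0.0442 paired; the ratios are the same.

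**Step 3: power for a small gain (2 points, SD 15, ρ = 0.5, 433 pairs).** The SE as written is 15 × 0.0680 = 1.02, so the test rejects beyond 1.96 × 1.02 = 2.00 points. The true SE is 15 × 0.0481 = 0.72.
- One-way ANOVA: Φ((2 − 2.00)/0.72) ≈ 50%
- Paired: Φ(2/0.72 − 1.96) ≈ 79%

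**Step 4: power for a gain of one item (5 points).** One-way ANOVA at ρ = 0.5 and 433 pairs: Φ((5 − 2.00)/0.72) = Φ(4.2), above 99.9%. It is also above 99.9% at ρ of 0.3 and 0.7. At 307 pairs it stays above 99.5%. For a 3-point gain at 433 pairs it is 88% to 96% across the three correlations.

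**Step 5: Friedman with two occasions.** Without ties its statistic is (2m − n)²/n, where m is the number who improved. This is the sign-test statistic. In simulation (307 pairs, 4,000 runs, ρ 0.3 to 0.7) it kept its level (0.046 to 0.054). Where the paired t-test had about 80% power, Friedman had about 62% and the Wilcoxon signed-rank 78% to 79%.

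**The case against.** **Repeated-measures ANOVA may have been meant.** Friedman is its usual rank counterpart, and the same section uses Kruskal–Wallis to compare cadres, so the authors seem to distinguish related from independent samples. This is a fair reading of intent. But the text says 'one way' and names no subject term, and an analyst following it would run the unpaired test. If the paired form was meant, the wording still needs correcting, and the Friedman branch would still give no mean gain.

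**The error is on the safe side.** This stands. With positive correlation, no route inflates false positives, and step 4 shows that the power loss matters only for gains below about one question.

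**A paired test is already in the plan.** This stands in part. The Wilcoxon signed-rank test is assigned to the cadre analysis, with medians and interquartile ranges. It does not supply the overall mean difference.

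**The comparison is not the study's main objective.** Correct: that is feasibility, and the sample size rests on a proportion. The comparison is still the sole stated hypothesis and the first specific objective.

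**A stronger reading that does not hold.** A reader might infer that the normality test will almost always reject scores on a 5-point grid and so force the Friedman branch. For normal scores rounded to that grid, this depends entirely on how ties are ranked. Shapiro–Francia rejected about 99% to 100% of samples when ties got arbitrary distinct ranks, and only about 1% to 3% when ties got averaged ranks. The protocol does not fix this, and it also consults histograms. Which branch would be used cannot be predicted from the document.

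**Conclusion.** The point holds in a limited form. As written, the parametric branch ignores the pairing and overstates the standard error by 1.20 to 1.83 times for assumed correlations of 0.3 to 0.7. The fallback is valid but less efficient, and it gives no mean change or interval. The size depends on a correlation and an SD that the protocol does not give. At zero correlation the problem with the parametric branch disappears, and with negative correlation it would reverse.

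A reader might infer that a positive result from this plan would be untrustworthy. The documents do not support that: under positive correlation a significant result would be, if anything, understated. What is at risk is the width of the interval and the reading of a small or null result.

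**What to change.** In Statistical analysis and in the abstract, replace the choice between one-way ANOVA and Friedman, and the normality test that governs it, with one stated estimate: the mean within-person change (3-month minus pre-training percentage score) with its 95% CI. A paired t-test is enough. Repeated-measures ANOVA or a mixed model with a participant effect gives the same answer when every trainee has both scores; session and site terms are optional and not needed to cure this fault. Extend the Wilcoxon signed-rank test, already planned for the cadre analysis, to the overall paired differences as the sensitivity analysis.

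The cost is one reworded paragraph and one abstract sentence. No new data are needed, and the sample size is unaffected because it rests on a proportion.
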